### Potential Risks

The potential risks to patients are related to the administration of oral HA, AKBA, and the rescue medicine (paracetamol). Although oral HA has no documented side effects, some users reported skin rashes and blurred vision after oral HA administration. These reports were anecdotal. In rare cases, HA (only if administered via IA) may cause allergic reactions [11].

In rare cases, AKBA may cause life-threatening allergic reactions, which can be identified by symptoms such as chest pain, breathing difficulties, hives, or swelling. Although AKBA is generally well tolerated, it may cause stomach discomfort, nausea, heartburn, fullness, or diarrhea [30].

Considering that the rescue medication paracetamol could be used only occasionally (high doses and prolonged treatment are not allowed in this study, and pre-existing renal and hepatic impairment are in the exclusion criteria), the potential risk should be low. In any case, the possible risks of this drug include hypersensitivity reactions (transient rash, paresthesia, and pruritus), thrombocytopenia (generally asymptomatic, rarely bleeding or bruising, black and soft stools, blood in urine and feces, and red spots on the skin), agranulocytosis (pharyngitis and fever, unexpected), dermatitis, hepatic impairment (conjunctival jaundice or skin current), renal colic with sudden onset of severe lumbar pain, and renal impairment (oligoanuria).

### Outcomes

#### Primary Outcomes

ROM: The improvement in active and passive knee flexion and extension, measured in degrees using a goniometer and assessed by the investigator, between the BL visit and the final visit.Ultrasound: A qualified physician records improvements in ultrasound parameters including synovial fluid, articular cartilage damage, medial meniscus protrusion, lateral meniscus protrusion, medial osteophytes, lateral osteophytes, enthesopathies, and effusions.VAS: The improvements in VAS (at rest) scores between the BL and final visit are measured in millimeters. A paper printed scale of 100 mm was used to measure pain intensity. Patients must draw a vertical line at the point considered to be the level of pain at a specific moment, that is, resting, moving, or pressing.Safety: Investigators must collect and evaluate all AEs and SAEs according to the current local legislation. AEs and SAEs must be summarized based on the number of affected patients. This includes related AEs, including those that are possibly related to or not evaluable. The incidence, type, and severity of AEs or SAEs are presented in frequency tables using MedDRA (Medical Dictionary for Regulatory Activities) terms. Frequency is compared using the χ^2^ test

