**Objective:**

The main goal of this pilot study with oral hyaluronic acid is to evaluate the feasibility of using objective tools as outcomes to evaluate improvements in knee mobility. We propose ultrasound and range of motion measurements with a goniometer that could objectively correlate changes in joint mobility with pain reduction, as assessed by the visual analog scale. The secondary objective is to collect data to estimate the time and budget for the main double-blind study randomized trial. These data may be quantitative (such as enrollment rate per month, number of screening failures, and new potential outcomes) and qualitative (such as site logistical issues, patient reluctance to enroll, and interpersonal difficulties for investigators).

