### Objectives

The primary objective of this pilot study is to test the same outcomes that will be implemented in the future RCT. This next trial will have a calculated sample size of at least 80 patients and a study duration of 4 months. Therefore, the feasibility of using ultrasound and range of motion (ROM) to objectively measure the potential improvement in the tested joint mobility during the trial is evaluated. Additionally, we investigate whether there is a correlation between ROM or ultrasound improvement and subjective VAS scores.

This pilot study, even if it is a small-scale investigation, should also confirm the safety data belonging to the large use of oral HA in clinical practice.

Another objective is to collect data to assess the feasibility of the future main RCT in advance, estimating the time and budget required. The collected data can be both quantitative and qualitative.

Finally, this study should provide preliminary data on the efficacy of the tested product. However, these data will not be exhaustive, as the focus of the pilot study is on the reliability of the outcome and feasibility of measurement, rather than statistical significance [29].

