#### Exploratory Outcomes

In addition to the primary and secondary outcomes, we identify exploratory outcomes that could be implemented in the main trial:

Actigraphy: This specific tool measures physical activity levels using a triaxial accelerometer that collects 24/7 data points during the patient’s daily activities. The investigator downloads and processes the data using specific software during routine visits at the center. The instrument is available in the market and has already been tested in OA clinical trials to objectively evaluate the composite measurement of pain and basic activities such as walking or performing daily tasks [31,32]. In this pilot study, an actigraph is worn around the knee to record data for 7 days.Rescue medication: Measuring the use of rescue medication during a clinical trial can provide information on the robustness of the analgesic efficacy of the tested product. Rescue medication may also be used as a primary end point according to the US Food and Drug Administration guidelines [33].

This study also provides preliminary data on the efficacy of the tested product.

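### The primary question is whether ROM and ultrasound are feasible measures, but apart from safety the primary outcomes, like the progression rule, record only improvement

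*Protocol article*

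**What the plan says.** **The question.** In the Abstract (Objective), the main goal "is to evaluate the feasibility of using objective tools as outcomes to evaluate improvements in knee mobility". Methods, Objectives says that "the feasibility of using ultrasound and range of motion (ROM) to objectively measure the potential improvement in the tested joint mobility during the trial is" under assessment. It adds that "the focus of the pilot study is on the reliability of the outcome and feasibility of measurement, rather than statistical significance". The same section lists product efficacy last and calls those data preliminary.

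**The primary outcomes.** Methods, Primary Outcomes lists four:
- ROM: "ROM: The improvement in active and passive knee flexion and extension, measured in degrees using a goniometer and assessed by the investigator", from baseline to final visit.
- Ultrasound: "A qualified physician records improvements in ultrasound parameters including synovial fluid, articular cartilage damage" and six further features.
- VAS: "The improvements in VAS (at rest) scores between the BL and final visit are measured in millimeters".
- Safety: "Investigators must collect and evaluate all AEs and SAEs according to the current local legislation".

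**The decision.** Secondary Outcomes, repeated in the Discussion, allows the main trial to proceed if VAS at rest and at least one objective outcome (ROM or ultrasound) have improved at the final visit. A significant correlation between them is not required.

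**Related text.** Secondary Outcomes names the choice of end points and their measurement among the parameters for estimating time and budget, without defining them. Statistical Analysis looks for Spearman correlations of at least 0.7 between the fall in VAS and the ROM or ultrasound changes. It provides for a check of data quality and completeness before analysis, and leaves missing values unreplaced.

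**The concern.** Whether a measurement can be obtained and whether it improves on treatment are different questions. Every enrolled patient could have complete ROM and ultrasound readings with no change between visits. Equally, the patients who were measured could improve while readings failed in others. A primary result made of change scores does not separate these cases. With no control group, the changes may also reflect natural course, regression to the mean or rescue medication.

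At stake is the decision on an 80-patient randomized trial that is to use the same outcomes. As written, that trial could start without any stated evidence that its objective end points can be collected, or be dropped although they can.

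**Working it through.** **1. The plan's own figure.** Sample Size sets the pilot at 10% of the main trial: 0.10 × 80 = 8. This reproduces. The article gives no power, effect size or SD for the pilot, so the main check is a comparison of texts.

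**2. Question against outcomes.**

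| Item | What it measures | Shows whether ROM or ultrasound can be obtained? |
|---|---|---|
| Primary: ROM | change in degrees | no |
| Primary: ultrasound | improvement in 8 listed features | no |
| Primary: VAS at rest | change in mm | no |
| Primary: safety | AEs and SAEs | no (serves the safety aim) |
| Secondary: choice of end points, measurement | undefined; for time and budget | possibly, but neither defined nor primary |
| Correlation with VAS | association of changes | no (an additional aim) |
| Progression rule | improvement in VAS plus one objective outcome | no |

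**3. What happens to a failed measurement.** A change score needs a reading at both visits. Missing values are not replaced, so a patient who lacks one reading leaves the analysis of that measure. The failure is visible only indirectly, in the number analysed.

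**4. Does the progression rule stand in for feasibility?** The article sets no size of improvement. Assume that any improvement in the mean counts, that there is no true change, and that mean changes are symmetric around zero. With k independent objective measures,

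P(go) = 0.5 × (1 − 0.5^k).

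- k = 2 (one composite each for ROM and ultrasound): 0.5 × (1 − 0.25) = 0.375.
- k = 12 (active and passive flexion and extension = 4, plus 8 ultrasound features): 0.5 × (1 − 0.5^12) = 0.4999.

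Simulation with a common correlation of 0 to 0.8 among all measures, VAS included, gives 0.38 to 0.45 for k = 2 and 0.49 to 0.50 for k = 12. Passing the rule is therefore weak evidence of improvement, and it contains no term for measurements obtained.

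**5. Does the correlation stand in for feasibility?** For r = 0.7 and n = 8, the Fisher interval is tanh(atanh 0.7 ± 1.96/√5) = tanh(0.867 ± 0.877), or about −0.01 to 0.94. (This standard error is for a Pearson coefficient. The variant for Spearman, √(1.06/5), gives −0.04 to 0.94.) A correlation at the plan's own threshold would settle little, and it too uses only patients with both readings.

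**6. What a direct feasibility outcome would give.** Let x of 8 enrolled patients have an evaluable measurement at both visits. The exact (Clopper-Pearson) limits are the 2.5% point of Beta(x, 9 − x) and the 97.5% point of Beta(x + 1, 8 − x). The upper limit is 1 when x = 8.

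| x of 8 | Proportion | Exact 95% interval |
|---|---|---|
| 8 | 100% | 63% to 100% |
| 7 | 87.5% | 47% to 99.7% |
| 6 | 75% | 35% to 97% |

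For 8 of 8 the lower limit is 0.025^(1/8) = 0.631.

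**The case against.** The best defence starts from the opening of Methods, Objectives, where the primary objective is to try out the outcomes intended for the randomized trial. On that reading, feasibility means that the tools register change and follow VAS, which needs the change scores. This stands in part. The change scores have a real use in the correlation analysis and should be kept. But that analysis is introduced as an additional aim, is not listed as a primary outcome, and need not be significant for the main trial to proceed. The same section also names reliability and feasibility of measurement as the focus.

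A reader might go further and infer that the article labels the same improvements primary in one place and exploratory in another. The text does not support this. Objectives calls the efficacy data preliminary, not exploratory. The closing line of Exploratory Outcomes, "This study also provides preliminary data on the efficacy of the tested product", names neither ROM, ultrasound nor VAS improvement. Preliminary data can come from a pilot's primary outcomes.

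Two further points have some force:
- The number analysed per measure would reveal completeness, and completeness is to be checked before analysis. But neither is a stated outcome, and neither enters the decision.
- An article leaves operational detail, such as what makes a scan readable, to the full protocol. That detail is not the complaint. The article itself states the primary outcomes and the progression rule, and these do not match its stated question.

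**Conclusion.** The mismatch holds in a limited form. The primary question is feasibility, with reliability. The non-safety primary outcomes and the progression rule are about improvement, and no stated primary outcome shows whether ROM and ultrasound can be obtained. This should be corrected. It does not invalidate the data collected, and the change scores remain useful for the correlation aim and as preliminary efficacy.

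The conclusion rests on the text alone. The 38% to 50% chance of a favourable decision with no true change is an illustration that depends on the assumptions in step 4 of the working, chiefly that any mean improvement counts. The intervals in step 6 describe the proposed outcome. They do not measure an error in the plan.

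**What to change.** - **Add a primary feasibility outcome.** For ROM and for each ultrasound parameter, report the proportion of enrolled patients with a complete, evaluable measurement at both baseline and final visit, with an exact 95% interval. Use all enrolled patients as the denominator. Treatment ended in May 2018, so if the outcome is new, identify it as added after data collection.
- **Relabel the improvements.** Present the ROM, ultrasound and VAS changes as preliminary efficacy estimates with intervals, and keep them for the correlation analysis.
- **Extend the progression rule.** In Secondary Outcomes and the Discussion, make the decision refer to the feasibility result as well as to improvement. Otherwise it would rest only on outcomes now labelled preliminary efficacy.

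The cost is wording in those sections and a count from data already collected. If the case report form did not record whether a scan was readable, count recorded values and say so. Report time per measurement only if it was recorded, since the article does not say that it was. There are three downsides. The interval at 8 patients is wide. The efficacy changes carry a lower label. The count also speaks to feasibility and not to reliability, which would need repeat readings that the article does not describe.

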### Study Design

This is an open-label, noncontrolled, single-center pilot feasibility study.

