### Intervention

All patients will receive Syalox 300 Plus (River Pharma), a food supplement containing HMWHA. Although this product has been available in European countries for several years and has been used in the clinical practice by hundreds of orthopedists, only a few clinical trials [18] have been conducted to test whether this type of product with oral HA could complement the treatment of patients affected by OA. In this study, the investigational product (IP) is administered as 1 tablet daily for 8 weeks, preferably before or during meals, with plenty of water. Following local legislation for food supplements, the product used is the same as that available in the market and must be administered as reported in the instruction for use. No changes in the dosage are planned during the study period. However, the investigator may decide to discontinue IP administration in case of adverse events (AEs) and serious AEs (SAEs) or to use other therapies at any time if he or she deems it necessary for the patient’s health. The reason for discontinuing the administration must be documented in both the source documents and CRF. At BL, each patient is given an IP package for the entire duration of the study (60 tablets). Patients are instructed to return all IP packages to the investigator at the end of the study to ensure product accountability. The IP contains 2 ingredients: HMWHA and dry extract of Boswellia.

A medical literature analysis has shown that HMWHA has been effective in relieving knee pain in various clinical trials without side effects [12,13]. The amount of HMWHA in the IP used in this study, which is greater than 2.8 million Da, is comparable to or slightly higher than that of supplements already available on the market for viscosupplementation in OA [13] and used in clinical trials [19-21].

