### Framework of the Study

Before any study procedure, patients receive information about the nature, purpose, benefits, and risks of the trial. Participants are then asked to sign an informed consent form. After the screening assessment (from day –14 to day 0), patients undergo a BL visit (day 0) to assess the inclusion and exclusion criteria and check for routine orthopedic conditions (Figure 3). To confirm the diagnosis of knee OA, the investigator evaluates an x-ray test with anteroposterior and lateral views that are no earlier than 6 months old.

At BL (Table 1), the investigator also performs an ultrasound, ROM test, VAS, and the KOOS questionnaire. The actigraph must be placed above the affected knee 7 days before the visit and removed at BL. Safety is assessed by phone at week 4 ± 2 days, or an optional visit should be conducted to complete the questionnaires, scales, and scores.

The final visit is scheduled for week 8 ± 4 days to conduct an ultrasound, ROM assessment, VAS, and the KOOS questionnaire. Patients wearing the actigraph will also be asked to return to the site 7 days before the visit to place the device above the affected knee; it will be removed during the final visit.

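### ROM and ultrasound are read unmasked in an open-label single-arm pilot, so reader expectation can enter the outcomes chosen for their objectivity

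*Protocol article*

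**What the plan says.** All references are to the protocol article.

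- **Aim.** The Abstract (Objective) says the pilot evaluates "the feasibility of using objective tools as outcomes to evaluate improvements in knee mobility". The Abstract (Background) says validity suffered in earlier trials because symptoms were measured only subjectively. The Rationale lists avoiding bias in the choice and measurement of end points among the reasons for a pilot.
- **Design.** Study Design: "This is an open-label, noncontrolled, single-center pilot feasibility study". Intervention: "All patients will receive Syalox 300 Plus (River Pharma), a food supplement containing HMWHA".
- **ROM.** Under Primary Outcomes, the improvement in active and passive flexion and extension is "measured in degrees using a goniometer and assessed by the investigator, between the BL visit and the final visit".
- **Ultrasound.** Under Primary Outcomes: "A qualified physician records improvements in ultrasound parameters including synovial fluid, articular cartilage damage". Six further parameters follow, making eight in all. No unit or grade is attached to them there.
- **Who and when.** Framework of the Study says that at baseline "the investigator also performs an ultrasound, ROM test, VAS, and the KOOS questionnaire". It then says: "The final visit is scheduled for week 8 ± 4 days to conduct an ultrasound, ROM assessment, VAS, and the KOOS questionnaire".
- **Use.** Under Secondary Outcomes, the main trial goes ahead if VAS at rest and at least one of ROM and ultrasound improve. No size of improvement is stated. Statistical Analysis looks for Spearman correlations of at least 0.7 between VAS reduction and each of ROM and ultrasound.
- **Limitations.** Limitation of the Study names the missing control group, the combination product and the choice of KOOS. It does not name unmasked assessment.

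**The concern.** A goniometer or an ultrasound probe makes an outcome objective only as far as the reading is independent of what the reader hopes to see. Here every patient is treated, and the second reading is taken at the end-of-treatment visit. At baseline the person who takes the ROM may also know the pain score. The wording of the ultrasound outcome adds to this. It names improvement, and not a value, as the thing recorded, and it gives no step that separates the reading from the visit.

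Three uses of the data are exposed: the pilot's conclusion about whether the tools work as objective outcomes, the objective half of the go rule, and the correlations with VAS. The correlations could be inflated if one person's expectation touches both measures.

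**Working it through.** **1. What the assessor knows.** There is one arm and all patients receive the product, so treatment is known. Goniometry is done live at baseline and at week 8, so the visit is known too. The article does not say this in so many words; it follows from the schedule.

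**2. What is recorded.** ROM is in degrees and is compared between two visits, so it is a per-visit value that is then differenced. Table 1 places ultrasound at baseline and week 8 as separate examinations, and Statistical Analysis treats the variables to be correlated as ordinal or better. Both suggest per-visit grades. The outcome definition says improvements are recorded. The wording therefore allows two readings, per-visit grades or a direct rating of change, and the article does not choose between them.

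**3. Who reads the ultrasound.** Primary Outcomes says a qualified physician; Framework of the Study says the investigator at baseline. These may be the same person, but the two places should be reconciled.

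**4. The plan's own number.** Sample Size takes 10% of a main trial of 80: 0.10 × 80 = 8, which reproduces. Two ultrasound visits each give 8 × 2 = 16 examinations.

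**5. Illustration of sensitivity.** The article gives no SD and no reader error, so every shift below is an assumption. Let b be the reader shift divided by the SD of the change score, with no true change. Improvement is taken as a mean change above zero, because the go rule states no size.

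- P(mean improves) = Φ(b × √8).
- P(significant improvement), two-sided 5% paired t test: noncentral t with 7 degrees of freedom and noncentrality b × √8.

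| b (assumed) | P(mean improves) | P(significant improvement) |
|---|---|---|
| 0 | 50% | 2.5% |
| 0.25 | 76% | 8.9% |
| 0.5 | 92% | 23% |
| 1.0 | 99.8% | 68% |

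In degrees, for one ROM measure with an assumed SD of change of 6: SE = 6/√8 = 2.12. Shifts of 2, 3 and 5 degrees give Φ(2/2.12) = 83%, Φ(3/2.12) = 92% and Φ(5/2.12) = 99%.

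**6. The objective half of the go rule.** Suppose any one of 12 items may count (4 ROM, 8 ultrasound). By simulation with no true change and no shift, at least one item improves in about 78% of trials (assumed inter-item correlation 0.8) to over 99% (correlation 0). With a 0.25 SD shift the figures are about 94% to over 99%. The no-shift figures come from the lack of a stated size in the rule, which is a separate matter. Only the rise, for example from 78% to 94%, belongs to this point. None of these figures covers the VAS condition, which must also be met.

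**The case against.** The case against is substantial.

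- **The word may carry little.** The article uses improvement for VAS, ROM and ultrasound alike, and the first two are plainly values per visit. A reader might infer that the physician rates change directly while knowing which scan is the later one. The article does not say so, and Table 1 and Statistical Analysis point towards per-visit grades. A reader might also infer that ROM is scored as an improvement; it is read in degrees. This stands and narrows the point.
- **An article condenses.** Grading scales, image storage and CRF layout may be in the full protocol and are not counted as missing here. A masking step could be there too. What remains is how the article itself fixes the outcome and the setting in which it is read.
- **The missing control is admitted.** That covers natural course and treatment expectation in general. Masking to visit is a different safeguard, and it is available in a single-arm study.
- **The main trial will be double-blind with placebo.** Readers there will still know the visit, but the blinded control arm will deal with that. This is correct. It also means that the change seen in the pilot does not show how the tools behave when the reader does not know the treatment.
- **The go rule is not met by one objective outcome alone.** A reader might infer that it is. VAS at rest must improve as well.
- **The study is over.** Treatment ended on May 25, 2018, and analysis was planned for completion by the end of that year. This limits what can still be changed, but not what can be reported.

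**Conclusion.** The concern holds in a limited form. As the article is written, nothing separates the ROM and ultrasound readings from knowledge of treatment and visit, so expectation can enter the measures chosen to avoid subjectivity, the objective half of the go rule and the VAS correlations. The point is stronger for ultrasound, where the recorded quantity is left open, than for ROM.

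A reader might go further and infer that bias does enter, or that any improvement seen will be a reader effect. The document does not support that: it gives no data on reader error, and the illustrative percentages follow from the assumed SD and shifts. How far individual ultrasound items depend on the reader is a technical judgement that the article does not address. What the illustration does show is that, with 8 patients, a modest shift is enough to tip the direction of a mean. The change should be made; it is cheap, and the admitted lack of a control group does not replace it.

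**What to change.** 1. State that each ultrasound parameter is recorded as an absolute value or grade at each visit, with change computed at analysis. Name one ultrasound operator consistently in Primary Outcomes and Framework of the Study.
2. Where images are stored, have the same physician score the 16 examinations with patient and visit labels removed, in random order, before analysis. If analysis has already been done, report the masked re-read next to it.
3. Take ROM at the final visit without the baseline and VAS values in view.
4. Where steps 2 and 3 can no longer be carried out, add unmasked assessment to Limitation of the Study and do not describe the observed improvement as objective evidence. Carry steps 1 to 3 into the main trial, which is to use the same outcomes.

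**Cost.** A few hours of the same physician's time plus image labelling, with no extra staff or patient procedure. Stored images may be less informative than live scanning for some items; for those, use the live value recorded without sight of baseline. Masking is imperfect when the reader has already examined the 8 patients, and hiding the baseline sheet reduces expectation in ROM but does not remove it.

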### Sample Size

For feasibility and pilot trials, it is important to justify the sample size; however, a formal calculation may not always be necessary [34] and is often not reported. In fact, a pilot study is not a hypothesis testing study, and often its main purpose is to test the feasibility of the proposed approach. This involves testing quantitative parameters, such as outcomes and resources, as well as qualitative factors, such as QoL and logistical issues at the site.

Although some papers suggest a sample size of 12-20 participants for pilot studies, it is generally reported that 10%-20% of the main sample size is a reasonable number for conducting such trials [35]. Given that the sample size of our main RCT will be 80 patients and the exploratory nature of this pilot study, investigators have agreed to enroll only 8 participants.

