### Limitation of the Study

The main limitation of this study is the absence of a control group. In fact, to reduce costs and simplify the protocol, the placebo group was not included.

A second limitation is that the IP used does not contain HA alone, but a combination of HA and a very low amount of boswellic acid (10% AKBA). With such a low dose of AKBA, only 1 study [45] showed positive results for the treatment of OA. This study used a product that contains 14.4 mg of AKBA combined with a high dose of methylsulfonylmethane, a well-known SYSADOA. Therefore, it can be assumed that in the pilot study, the effect of HA should be more prevalent than that of AKBA.

Finally, the KOOS questionnaire is used in this pilot study, although the WOMAC is the most widely used test for evaluating hip and knee OA. The KOOS evaluates both the short- and long-term consequences of knee injuries. The KOOS is selected for this study as it is a free and open-access alternative to the expensive WOMAC index. The KOOS is an extension of the WOMAC.

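### Adverse-event frequency is to be compared by chi-square although the single group of 8 offers no valid comparison, and the aim of confirming safety exceeds what 8 patients can show

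*Protocol article*

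**What the plan says.** All places are in the protocol article.

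- **Primary Outcomes (Safety).** AEs and serious AEs are counted by patient, and their incidence, type and severity are tabulated by MedDRA term. The item then ends: "Frequency is compared using the χ^2^ test". It does not say what is compared with what.
- **Statistical Analysis.** Categorical variables are described by frequencies and percentages and compared by chi-square, again with no groups named. The same section removes from the analysis the data of participants who violated the eligibility criteria and makes no exception for safety.
- **Study Design.** "This is an open-label, noncontrolled, single-center pilot feasibility study".
- **Intervention.** "All patients will receive Syalox 300 Plus (River Pharma), a food supplement containing HMWHA".
- **Limitation of the Study.** "The main limitation of this study is the absence of a control group".
- **Sample Size.** "investigators have agreed to enroll only 8 participants". The same section says that a pilot does not serve to test hypotheses.
- **Objectives.** The pilot "should also confirm the safety data belonging to the large use of oral HA in clinical practice". A clause before this admits that the investigation is small.

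No section gives an expected AE rate or a historical rate for comparison.

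**The concern.** A chi-square test of frequency needs either two or more groups or a reference rate. The article names neither, and its design supplies no second group. An analyst who follows the text would have to invent a contrast, and any p-value from it would have no defined meaning.

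The second issue is the word *confirm* in the safety objective. The Conclusions of the Abstract list safety among the items to be evaluated for the future trial, so the result is meant to be used. If few or no events occur in 8 patients over 8 weeks, that wording invites more reassurance than the data can carry.

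**Working it through.** **Inputs.** From Sample Size: n = 8 and a main trial of 80. From Study Design and Intervention: one arm. From Table 1: AEs are recorded at three visits. The article gives no AE rate, so the 5% and 10% used in step 4 are assumptions for illustration. The minimum expected count of 5 is the customary rule of thumb for the chi-square approximation.

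**1. The plan's own figure.** The article sets the pilot size as a share of the main trial: "it is generally reported that 10%-20% of the main sample size is a reasonable number for conducting such trials", and "Given that the sample size of our main RCT will be 80 patients". The lower end is 0.10 × 80 = 8, so the stated size reproduces. It has no basis in safety precision.

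**2. Is there any valid chi-square contrast?** The possible readings are:

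- *Between arms.* There is only one arm.
- *Patient subgroups.* Take subgroups of size a and 8 − a, with e of the 8 patients having an event. The smallest expected cell is min(a, 8 − a) × min(e, 8 − e) / 8. Its largest possible value is 4 × 4 / 8 = 2.
- *Visit against visit.* This gives 8 and 8 observations on the same patients. With e event observations out of 16, the smallest expected cell is 8 × min(e, 16 − e) / 16, at most 8 × 8 / 16 = 4. The data are also paired, so a chi-square test for independent samples does not apply.
- *Against an external rate p.* None is stated. If one were supplied, the smallest expected count would be 8 × min(p, 1 − p), at most 4.

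Every reading falls short of 5.

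**3. What 0 events in 8 would show.** The exact upper limit solves (1 − p)^8 = α.

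- One-sided 95%: 1 − 0.05^(1/8) = 0.312, or 31.2%.
- Two-sided 95% (Clopper-Pearson): 1 − 0.025^(1/8) = 0.369, or 36.9%.

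With 1 event in 8, the two-sided exact interval runs from 0.3% to 52.7%. With 2 in 8, it runs from 3.2% to 65.1%.

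**4. Chance of seeing no case at all**, (1 − p)^8:

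| Assumed true rate | No case among 8 | At least one case |
|---|---|---|
| 5% | 0.95^8 = 66.3% | 33.7% |
| 10% | 0.90^8 = 43.0% | 57.0% |

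For comparison, a one-sided 95% upper limit of at most 10% after zero events needs ln(0.05) / ln(0.90), rounded up to 29 patients. For at most 5% it needs ln(0.05) / ln(0.95), rounded up to 59.

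**5. Effect of the eligibility exclusion.** If one dosed patient were removed as a violator, the two-sided limit for zero events would become 1 − 0.025^(1/7) = 41.0%, and any AE in that patient would be lost from the tables.

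**The case against.** The strongest reply is that the chi-square sentence is a leftover at the end of a sound descriptive plan. Counts of patients with events and tables by type and severity are already prescribed, and frequencies and percentages appear again under Statistical Analysis. The article disclaims hypothesis testing, names the missing control group as its main limitation, and qualifies the safety aim by the small scale of the study. The rule for proceeding to the main trial (Secondary Outcomes) uses only pain at rest and the objective measures. All of this stands, and it limits the impact. It does not give the test a comparator, and the qualifier admits the small size while keeping the claim to confirm.

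Three stronger readings are tempting, and the documents do not support them:

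- A reader might infer that the safety analysis consists of the chi-square test alone. It does not; the test is added to planned tables.
- A reader might infer that every possible chi-square here would use dependent counts. Visit comparisons would, but patient subgroups would give independent counts. Their problem is that the expected cells are too small.
- A reader might infer that a clean result will be reported as proven safety and carried into the main trial's risk statement. No section says so. The article's own Potential Risks section rests on literature and anecdotal reports and does list harms.

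An exact confidence interval is a detail that an analysis plan may well contain. Its absence from the article is therefore not the fault; the stated test is.

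**Conclusion.** The point holds in limited form. The chi-square comparison of AE frequency is wrong as written: the trial has one group of 8 and no reference rate, and no contrast that could be built within it reaches an expected count of 5 (at most 4 for visits, which are also paired, and at most 2 for subgroups). The aim to confirm the safety data is beyond 8 patients, since zero events leaves true rates up to 36.9% (two-sided 95%) or 31.2% (one-sided 95%) open. These limits assume only that the 8 patients are independent and share a common event probability; they need no outside figure. The consequence is modest: a meaningless p-value and an overstated objective, with no effect on the decision to proceed.

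**What to change.** 1. In Primary Outcomes, delete the sentence prescribing a chi-square comparison of AEs.
2. In Statistical Analysis, limit the chi-square rule for categorical variables so that it does not apply to AEs. Otherwise the general rule brings the deleted test back.
3. Keep the planned descriptive tables, and add an exact (Clopper-Pearson) 95% confidence interval to the number and percentage of patients with each AE and serious AE.
4. Base these on all dosed patients, and exempt safety from the exclusion of eligibility violators.
5. In Objectives, replace *confirm* with *describe*. If no events are seen, state that this excludes only true rates above about 37%.

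The cost is a few sentences of text, with no new data and no change to study procedures. Treatment ended in May 2018 and the analysis was planned for that year, so the change now falls on the analysis and report and should be declared there as a departure from the published plan. The downside is a less favourable safety statement.
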